### Statistical methods

The primary analysis will use the number of binge eating episodes during the last four weeks in a linear mixed model with baseline adjustment at T8 and T9. In case of non-normally distributed data we want to use generalized linear mixed models as this statistical approach accounts for non-normally distributed data better. To test for noninferiority of the inhibitory control training without feedback compared to the inhibitory control training with feedback, we perform one tailed-tests with an alpha-level of 0.025. Further, we compare if the confidence interval of the inhibitory control training without feedback includes the effect of the inhibitory control training with feedback which resembles the non-inferiority margin [3, 37, 53]. For comparison of inhibitory control training with feedback against the waitlist control and for the comparison of inhibitory control training without feedback against the waitlist control we conduct two-sided tests with an alpha-level of 0.05.

In secondary analyses, a mixed model approach will be used to analyze the secondary outcomes also with baseline adjustment. Effect sizes will be analyzed and reported for primary and secondary outcomes. For binary outcomes, odds ratios and for quantitative outcomes, standardized differences will be reported. Primary parameters will be time vs. treatment interactions at several time points after baseline.

Further, for the regression analyses, a mixed model approach will be used as well. We want to investigate the impact of sociodemographic, comorbid psychopathology (SKID-V, BDI-II), self-efficacy (URICA-S, IE-4, food-related self-efficacy), self-esteem (RSE), treatment expectation (self-developed self-report questionnaire) as predictors on the primary outcome.

Last, for potential mechanisms underlying the inhibitory control training, we will conduct mixed models on the valence ratings of the different food stimuli and its relation to the primary outcome.

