There will be no interim analysis. The primary analysis will be done for the intent to treat population, which is defined by including all patients who attended the baseline assessment. Multiple imputation will be used for subjects dropping out according to the method of Rubin. The imputation model will use 500 replications and will include age, gender and baseline assessment. Furthermore, available values from preceding visits will be included. Analyses will be performed using SPSS for Windows (Version 28.0.0.0) and R (Version 4.2.2.) using the packages *lme4* [6], *lmerTest* [34] and *emmeans* (Lenth, 2019).

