A deeper understanding of underlying mechanisms driving the effectiveness of cognitive trainings is of particular interest. Several potential pathways have been proposed, for example the *devaluation effect* of food stimuli [56], healthy food choices [30] but also eating-disorder-specific traits [10, 16]. Additionally, unspecific traits like self-efficacy, metacognitive self-regulation and self-esteem may also predict positive treatment outcomes [44]. To get a broad view on several variables that might be causal in the treatment outcome we included several variables related and unrelated to the eating disorder to allow for conclusions on effective treatment based on individual predispositions.

Nonetheless, the current trial faces several challenges: In the previous RCT, participants had a 50 percent chance of receiving real transcranial direct current stimulation (tDCS) and still received the inhibitory control training when assigned to the placebo tDCS, which likely enhanced overall acceptability. In contrast, participant engagement in the present trial may be more difficult to ensure, as only the training or a waitlist condition are provided. Moreover, the training alone may not fully address the necessity of multimodal treatment which is demanded by severity of BED and BN [25]. Further, to work out the importance of food-specific ICT, it might make sense to consider another control group instead of a waitlist group: a group receiving a sham training, e.g. ICT with neutral/non-food specific stimuli, could meet these criteria. Last, of study patients might be challenging, in particular to distinguish the effect of the two-weeks ICT intervention from longer-termed concomitant care.

If the training without feedback, i.e. without eye tracking, proves effective in reducing binge eating frequency to a clinically meaningful degree, and ideally achieves outcomes comparable to the training with feedback, this could pave the way for an economically viable digital intervention. Moreover, findings from this trial, including regression analyses, will allow us to examine how sample characteristics influence the effectiveness of inhibitory control training and assess its suitability for potential home-treatment. With the identification of fruitful elements of effective inhibitory control training, the foundation stone is laid for the development of app-based smartphone interventions, which already have a place in basic care of mental disorders [47].

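### The stated imputation model omits randomised arm, which pulls training-versus-waitlist effects towards zero: slightly at the planned 5% dropout, more if dropout is higher

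*Protocol article*

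**What the plan says.** All of this is in the protocol article, Statistical methods, unless another section is named.

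- Population: "The primary analysis will be done for the intent to treat population, which is defined by including all patients who attended the baseline assessment".
- Handling of dropouts: "Multiple imputation will be used for subjects dropping out according to the method of Rubin".
- Imputation model: "The imputation model will use 500 replications and will include age, gender and baseline assessment". The next sentence adds: "Furthermore, available values from preceding visits will be included".
- Analysis model: a "linear mixed model with baseline adjustment at T8 and T9". On the target of estimation: "Primary parameters will be time vs. treatment interactions at several time points after baseline".

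No section adds arm to the imputation model or says that imputation is done within arm. According to Table 1 and the section on the primary outcome, the four-week EDE binge count is taken at T0, T8 and T9, but not at T7. A seven-day count is taken at T7 and T8. The Participant timeline gives the waitlist arm four appointments, so it has no T1-T6 session data.

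**The concern.** An imputation model should contain the variables of the analysis model, above all the one whose effect is being estimated. If arm is left out, a waitlist dropout is imputed partly from trained patients' outcomes, and a trained dropout partly from untrained ones. The imputed share of each arm then carries little or none of the true difference.

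Earlier-visit values bring back some arm information, but only for patients who reached such a visit. Because the analysis set includes everyone seen at baseline, a patient lost straight after randomisation is imputed from age, gender and baseline alone. Anyone lost before T8 has no earlier post-baseline value of the primary outcome itself. At stake are the two superiority comparisons with waitlist and, less predictably, the non-inferiority comparison.

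**Working it through.** **Inputs from the protocol.** 21 patients per arm, 1:1:1 allocation, 5% dropout, and an effect of about 0.7 SD (Sample size). That effect is for treatment against an active comparator in the pilot; here it only illustrates training against waitlist. The plan's own total reproduces: 20 × 1.05 = 21, and 21 × 3 = 63. Expected dropouts are 21 × 0.05 = 1.05 per arm, about 3 in all.

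**Assumptions.** Normal outcome with unit SD; baseline-outcome correlation 0.5; true benefit over waitlist 0.70 SD with feedback and 0.40 SD without; dropout at random, equal across arms unless stated. The 10% and 20% dropout rates are not in the documents.

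**Step 1: formula.** Suppose a fraction f of each arm is imputed without arm or any post-baseline value. The imputed patients then have the same expected outcome in every arm, given baseline. The expected contrast is (1 − f) × δ + f × 0 = (1 − f) × δ:

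- 5%: 0.95 × 0.70 = 0.665
- 10%: 0.90 × 0.70 = 0.63
- 20%: 0.80 × 0.70 = 0.56

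**Step 2: simulation.** 1,500 trials per setting, 20 imputations, Rubin's rules, baseline-adjusted analysis. Entries are the mean estimate for feedback versus waitlist, with power in brackets (share of runs with estimate/SE beyond ±2.0).

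| Dropout | No post-baseline value: arm omitted | No post-baseline value: arm included | T7-type value: arm omitted | T7-type value: arm included |
|---|---|---|---|---|
| 5% | 0.66 (65.3%) | 0.70 (69.7%) | 0.69 (69.9%) | 0.70 (71.1%) |
| 10% | 0.62 (56.8%) | 0.69 (68.1%) | 0.67 (65.9%) | 0.70 (68.1%) |
| 20% | 0.54 (38.9%) | 0.69 (59.5%) | 0.64 (58.9%) | 0.69 (63.1%) |

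The T7-type value carries the full treatment effect and has a residual correlation of 0.6 with the outcome; both are assumptions. Repeat runs of the arm-omitted worst case gave 0.66 to 0.67, 0.62 to 0.63 and 0.54 to 0.56, in line with the formula.

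**Step 3: gap between the training arms, equal dropout.** The true gap is 0.30. With arm omitted and no post-baseline value it is estimated at 0.28, 0.27 and 0.22; with arm included, at 0.30, 0.29 and 0.28.

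**Step 4: false non-inferiority rate.** The nominal rate is 2.5%, since "we perform one tailed-tests with an alpha-level of 0.025". The protocol gives no numerical margin, so two were assumed (4,000 runs per setting, 15 imputations, arm omitted, no post-baseline value):

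- Margin 0.35 SD: 2.2%, 1.9% and 2.3% at 5%, 10% and 20% dropout.
- Margin 0.70 SD: 3.0%, 3.2% and 3.8%.

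The simulation error of such a rate is about √(0.025 × 0.975 / 4,000) = 0.25 points. The smaller margin therefore shows no inflation and the larger one mild inflation. Arm-blind imputation also makes Rubin's standard error too large, which offsets the shrinkage.

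**Step 5: unequal dropout.** Take both training arms at −0.70 against waitlist at 0 (lower is better), with 20% dropout without feedback and 5% in the other two arms.

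- Pooled observed mean: −0.70 × (0.95 + 0.80) / (0.95 + 0.80 + 0.95) = −0.454
- With feedback: 0.95 × (−0.70) + 0.05 × (−0.454) = −0.688
- Without feedback: 0.80 × (−0.70) + 0.20 × (−0.454) = −0.651

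No-feedback looks 0.037 SD worse although the arms are equal (simulated: 0.039), which counts against non-inferiority. Putting the 20% dropout in the feedback arm reverses the sign (simulated: −0.024).

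**The case against.** The strongest defence is size. At the planned dropout about one patient per arm is imputed. The standard error of an arm contrast is about √(1 − 0.5²) × √(2/20) = 0.27 SD, so a bias of 0.04 SD is about 0.15 standard errors. The larger figures need dropout rates that the protocol does not state. This stands and limits the severity. It does not remove the point, because the Discussion itself warns that "participant engagement in the present trial may be more difficult to ensure" than in the pilot from which the 5% was taken.

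Second, the plan does use earlier-visit values. This also stands: it cuts the loss at 5% dropout to about 0.01 SD, but only for patients who attended such a visit.

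Third, the text says what the model will include, not that nothing else will be used, and an analysis plan that is not shown may add arm. That is possible. But the article fixes the number of replications and names the predictors, so a programmer who follows it would leave arm out.

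A reader might go further and infer that every contrast shrinks by the missing fraction, or that the omission makes the non-inferiority test anti-conservative. The documents support neither. The first describes only patients lost before any post-baseline visit. The second depends on the margin, on whether no-feedback is truly worse and on the dropout pattern: steps 4 and 5 show settings with no inflation and with bias in the opposite direction.

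**Conclusion.** The point holds, with minor to moderate severity. As written, the imputation model omits the factor that the analysis estimates and biases the training-versus-waitlist contrasts towards zero. The worst-case loss is about 0.04 SD at 5% dropout, 0.08 SD at 10% and 0.15 SD at 20%; with a correlated post-baseline value it is about 0.01, 0.03 and 0.06 SD. Worst-case power falls by 4 to 5 points at 5% dropout, about 11 at 10% and about 21 at 20%. These sizes rest on the assumed 0.70 SD effect, the 0.5 baseline correlation, a normal outcome and dropout at random. For non-inferiority the direction is not settled. The estimated gap narrows when no-feedback is truly worse and dropout is equal, but no general rise in the error rate is shown.

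**What to change.** State that the imputation model includes randomised arm and arm by visit, or that imputation is done separately within each arm. Say which earlier-visit variables are used: those available in all arms (such as the seven-day count at T7 and the values at T8), with T1-T6 session values used only within the training arms. This costs one or two sentences, to be settled before the data are analysed by arm, and needs no further patients or data.

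Making the mixed model on observed data primary, or imputing with a count model, are options the team may consider on other grounds. Neither follows from this error.

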### Ethical aspects

Ethical approval for conducting the trials has been obtained by the ethics committee of the Medical Faculty and the University Hospital Tübingen (Reference Number 679/2023BO2). All trial patients provide written informed consent prior to inclusion into the study. Patients can withdraw from the trial an any point without any disadvantage. Patients receive monetary compensation (8€/h).

## Discussion

The MINDBinges trial aims to identify the underlying mechanisms of a food-related inhibitory control training for individuals suffering from regular binge eating, as seen in BED, BN, OSFED and UFED with regular binge eating behaviour. This trial seeks to enhance our understanding of factors predictive of effective treatment, thereby enabling the development of more targeted cognitive trainings that address specific facets of eating disorder pathology.

The primary aim of this trial is to disentangle the role of feedback and its clinical relevance within cognitive trainings. To the best of our knowledge, this is one of the first studies in the domain of eating disorders investigating the role of feedback on task performance on clinical outcomes. This study builds on findings from a previous clinical RCT, which demonstrated a significant strong reduction in binge eating in a clinical population following six sessions of the same food-related inhibitory control training [19]. As in the prior study, we employ an individualized training approach by selecting food stimuli according to personal preference. The primary outcome reflects high clinical relevance as binge eating frequency is the core pathology of the assessed eating disorders (American Psychiatric Association and Association, 2013). Importantly, a lived experience representative has been part of the study team from the beginning of the project and was involved in the conceptualization of the whole study, especially regarding the development of the research questions. The perspective of this lived experience representative on the role of feedback is summarized in Box 1. The role of feedback is hypothesized to have a valuable role in optimizing inhibitory control trainings. To assess longer-term changes, we also stick to a comparably long follow-up period, enabling conclusions on partial or full remission of study patients. Additionally, we also investigate the superiority of the treatment against a waitlist control which was absent in the previous trial. Finally, by adopting a transdiagnostic approach and using a broad range of questionnaires for an in-depth characterization of the study population which might offer chances in subgroup-typical specifics in adapting and increase specifity of cognitive trainings.

A deeper understanding of underlying mechanisms driving the effectiveness of cognitive trainings is of particular interest. Several potential pathways have been proposed, for example the *devaluation effect* of food stimuli [56], healthy food choices [30] but also eating-disorder-specific traits [10, 16]. Additionally, unspecific traits like self-efficacy, metacognitive self-regulation and self-esteem may also predict positive treatment outcomes [44]. To get a broad view on several variables that might be causal in the treatment outcome we included several variables related and unrelated to the eating disorder to allow for conclusions on effective treatment based on individual predispositions.

Nonetheless, the current trial faces several challenges: In the previous RCT, participants had a 50 percent chance of receiving real transcranial direct current stimulation (tDCS) and still received the inhibitory control training when assigned to the placebo tDCS, which likely enhanced overall acceptability. In contrast, participant engagement in the present trial may be more difficult to ensure, as only the training or a waitlist condition are provided. Moreover, the training alone may not fully address the necessity of multimodal treatment which is demanded by severity of BED and BN [25]. Further, to work out the importance of food-specific ICT, it might make sense to consider another control group instead of a waitlist group: a group receiving a sham training, e.g. ICT with neutral/non-food specific stimuli, could meet these criteria. Last, of study patients might be challenging, in particular to distinguish the effect of the two-weeks ICT intervention from longer-termed concomitant care.

If the training without feedback, i.e. without eye tracking, proves effective in reducing binge eating frequency to a clinically meaningful degree, and ideally achieves outcomes comparable to the training with feedback, this could pave the way for an economically viable digital intervention. Moreover, findings from this trial, including regression analyses, will allow us to examine how sample characteristics influence the effectiveness of inhibitory control training and assess its suitability for potential home-treatment. With the identification of fruitful elements of effective inhibitory control training, the foundation stone is laid for the development of app-based smartphone interventions, which already have a place in basic care of mental disorders [47].

With the data retrieved from the MIND BINGES trial, we contribute to the development of scientific well-founded treatment for individuals suffering from regular binge eating to achieve more sustainable abstinence from binge eating, even possibly being enhanced by the predictive power of subgroups being able to profit most from those intervention.

## Data Availability

No datasets were generated or analysed during the current study.
